### 6.6.2 Break code by sponsor in an emergency

In accordance with applicable regulations, in case of suspected, unintended, serious adverse reactions, and if consideration is given to blinded treatment, the treatment code of subject is usually broken before being reported to medical institutions, ethics committees, and researchers.

## 6.7 Post-study treatment

Multi-center, Randomized, Double-blind, Controlled Study of the Effectiveness and Safety of Mifepristone in Treating Adenomyosis

At the end of the study, subjects will receive standard therapy/treatment according to the researcher's decision.

## 6.8 Combining medication and treatment

(1) In addition to the trial drug, it is forbidden to use other Chinese and Western drugs treating this disease that are the same or similar to the functional indications of mifepristone tablets in the observation period, and other drugs and treatment methods that affect the evaluation of the efficacy of this trial, including other contraceptive drugs (such as progestin contraceptives, estrogen-progestin contraceptives, etc.); and drugs that interact with mifepristone (such as ketoconazole, itraconazole, erythromycin, etc., and rifampicin, corticosteroids, and some anticonvulsants, griseofulvin, non-steroidal anti-inflammatory drugs, and so on). Please refer to the instructions for drug interactions for details. It is forbidden to take painkillers and hemoglobin drugs privately without the consent of a doctor.

(2) During the study period, the endometrium thickness of the B-ultrasonic examination should be recorded in the eCRF. If the researcher suspects endometrial hyperplasia, hysteroscopy or curettage examinations can be performed if necessary, and with reference to clinical routine treatment, the study medication can be discontinued or continue to be used.

(3) During the observation period, the name, usage and dosage, and time of taking of drugs or other treatments that must be taken for other comorbid diseases, must be recorded in the electronic case report form.

## 7. Research steps and variables

### 7.1 Research steps

#### 7.1.1 The flow chart

Table 7-1 The flow chart of clinical research

| Interview           | Screening period | Baseline period | Double-blind treatment period |        |       | Follow-up period |
|---------------------|------------------|-----------------|-------------------------------|--------|-------|------------------|
| Number of interview | First            | Second          | Third                         | Fourth | Fifth | Sixth            |

Multi-center, Randomized, Double-blind, Controlled Study of the Effectiveness and Safety of Mifepristone in Treating Adenomyosis

| Interview                                     | Screening period | Baseline period | Double-blind treatment period |                              |                               | Follow-up period                |
|-----------------------------------------------|------------------|-----------------|-------------------------------|------------------------------|-------------------------------|---------------------------------|
| Time point of interview                       | -42~0 day        | 0~3 day         | The fourth week $\pm 4$ days  | The eighth week $\pm 4$ days | The twelfth week $\pm 4$ days | The sixteenth week $\pm 4$ days |
| Basic history collection               |                  |                 |                               |                              |                               |                                 |
| Signing informed consent                      | √                |                 |                               |                              |                               |                                 |
| Eligibility screening                         | √                |                 |                               |                              |                               |                                 |
| Filling in general information                | √                |                 |                               |                              |                               |                                 |
| Vital Signs/Anthropometrics                   | √                |                 | √                             |                              | √                             |                                 |
| Gynecological examination                     | √                |                 |                               |                              | √                             |                                 |
| The follow-up of auxiliary examination |                  |                 |                               |                              |                               |                                 |
| Blood routine                                 | √                |                 | √                             |                              | √                             | √                               |
| Coagulation function                          | √                |                 |                               |                              |                               |                                 |
| Liver and kidney function and blood           | √                |                 | √                             |                              | √                             |                                 |

Multi-center, Randomized, Double-blind, Controlled Study of the Effectiveness and Safety of Mifepristone in Treating Adenomyosis

| Interview                      | Screening period  | Baseline period | Double-blind treatment period |   |                   | Follow-up period |
|--------------------------------|-------------------|-----------------|-------------------------------|---|-------------------|------------------|
| lipids                         |                   |                 |                               |   |                   |                  |
| Three sex hormone tests        | √                 |                 | √                             |   | √                 | √                |
| CA 125              | √                 |                 |                               |   | √                 | √                |
| Blood/Urine HCG                | √                 |                 | √                             |   | √                 |                  |
| Pelvic B ultrasound            | √                 |                 | √                             |   | √                 | √                |
| Pelvic MRI                     | √(Non-essential)  |                 |                               |   | √(Non-essential)  |                  |
| Breast B ultrasound            | √                 |                 |                               |   |                   |                  |
| Leucorrhea routine             | √                 |                 |                               |   |                   |                  |
| ECG                            | √                 |                 |                               |   |                   |                  |
| Questionnaire follow-up |                   |                 |                               |   |                   |                  |
| VAS                            | √                 |                 | √                             | √ | √                 | √                |
| PBAC                           | √                 |                 | √                             | √ | √                 | √                |
| Other work              |                   |                 |                               |   |                   |                  |
| Endometrial biopsy             | √(when necessary) |                 |                               |   | √(when necessary) |                  |
| Dispensing trial drugs         |                   | √               | √                             | √ |                   |                  |

Multi-center, Randomized, Double-blind, Controlled Study of the Effectiveness and Safety of Mifepristone in Treating Adenomyosis

| Interview                                      | Screening period | Baseline period | Double-blind treatment period |   |   | Follow-up period |
|------------------------------------------------|------------------|-----------------|-------------------------------|---|---|------------------|
| Recording adverse events and drug combination  |                  |                 | √                             | √ | √ | √                |
| Compliance judgment (medication and follow-up) |                  |                 | √                             | √ | √ |                  |

#### 7.1.2 Assessment schedule

##### 7.1.2.1 Interview 1- Screening period (-42 to 0 day)

The following data is collected and the following assessments are performed 4 to 6 weeks before starting research drug treatment:

- (1) Signing informed consent (before conducting any other study-related assessment described below)
- (2) Eligibility screening (according to the inclusion criteria and exclusion criteria)
- (3) Filling in general information
- (4) Vital signs/Anthropometrics (blood pressure, heart rate, height, weight, gynecological examination)
- (5) Completion of related auxiliary examinations (blood routine, coagulation function, blood/urine human chorionic gonadotropin, CA125, liver and kidney function, blood lipids, three sex hormone tests, pelvic ultrasonography (uterine length, width, thickness), pelvic MRI (non-essential), breast B ultrasound, ECG, leucorrhea routine)
- (6) Distributing questionnaires (VAS, PBAC)
- (7) Endometrial biopsy (when necessary)

##### 7.1.2.2 Interview 2- Baseline period (0 to 3 day)

- (1) Improving auxiliary examinations

Multi-center, Randomized, Double-blind, Controlled Study of the Effectiveness and Safety of  
Mifepristone in Treating Adenomyosis

(2) Randomization group and dispensing study drugs

7.1.2.3 Interview 3- Taking medicine for 1 month (The fourth week  $\pm 4$  days)

- (1) Measurement of vital signs (blood pressure, heart rate)
- (2) Completion of related auxiliary examinations (blood routine, liver and kidney function, blood lipids, three sex hormone tests, blood/urine human chorionic gonadotropin, pelvic ultrasonography (uterine length, width, thickness))
- (3) Recording adverse events and drug combination
- (4) Compliance judgment
- (5) Distributing questionnaires (VAS, PBAC)
- (6) Dispensing study drugs

7.1.2.4 Interview 4- Taking medicine for 2 months (The eighth week  $\pm 4$  days)

- (1) Recording adverse events and drug combination
- (2) Compliance judgment
- (3) Distributing questionnaires (VAS, PBAC)
- (4) Dispensing study drugs

7.1.2.5 Interview 5- Taking medicine for 3 months (The twelfth week  $\pm 4$  days)

- (1) Vital signs/Anthropometrics (blood pressure, heart rate, height, weight, gynecological examination)
- (2) Completion of related auxiliary examinations (blood routine, liver and kidney function, blood lipids, three sex hormone tests, blood/urine human chorionic gonadotropin, CA125, pelvic ultrasonography (uterine length, width, thickness), pelvic MRI (non-essential))
- (3) Counting and recycling drugs
- (4) Recording adverse events and drug combination
- (5) Compliance judgment
- (6) Distributing questionnaires (VAS, PBAC)
- (7) The result of ultrasound shows endometrial thickness  $\geq 12\text{mm}$  or suspected abnormal endometrium, and endometrial biopsy is recommended.

Multi-center, Randomized, Double-blind, Controlled Study of the Effectiveness and Safety of Mifepristone in Treating Adenomyosis

#### 7.1.2.6 Interview 6- Drug withdrawal for 1 month (The sixteenth week $\pm$ 4 days)

(1) Completion of related auxiliary examinations (blood routine, CA125, three sex hormone tests, pelvic ultrasonography)

(2) Distributing questionnaires (VAS, PBAC)

(3) Recording adverse events and drug combination

## 7.2 Effectiveness

### 7.2.1 Visual Analogue Scale (VAS)

### 7.2.2 Pictorial blood loss assessment chart (PBAC)

Effectiveness variable - scored by PBAC - menstrual flow status prior to the assessment time point. At the same time, the uterine bleeding in the first 4 weeks was evaluated.

### 7.2.3 Changes in uterine volume

Effectiveness variable - uterus length, width, and thickness measured by B-ultrasound, volume (cm^3) = length x width x thickness x 0.5236 - changes of the uterine volume were compared within group before and after treatment (0, 12, 24 weeks and follow-up period).

### 7.2.4 Anemia improvement

The changes of anemia related indicators (red blood cell count, hemoglobin) relative to baseline of each interview in each group are described and compared within group before and after treatment (0, 4, 12, 16weeks).

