## 2. Research purposes

The main purpose of this study was that the visual analogue scale (VAS) was used as the main evaluation index to investigate whether daily oral mifepristone of 10 mg was superior to placebo in the treatment of symptoms of adenomyosis-associated pelvic pain.

The secondary purpose is to evaluate the pictorial blood loss assessment chart (PBAC), uterine volume, hemoglobin changes, and the safety of this dose (eg, adverse events, vagina bleeding, gynecological safety).

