### 4.3 Rationality of research design

In order to avoid selection bias or bias by any other investigators' or subjects' understanding of the treatment used, the trial design was performed according to the principles of randomization, allocation concealment, double-blind, placebo control. The placebo control is necessary because of the more pronounced placebo effect observed in literature studies.

Multi-center, Randomized, Double-blind, Controlled Study of the Effectiveness and Safety of Mifepristone in Treating Adenomyosis

From an ethical point of view, placebo-controlled trials are considered acceptable because they allow the patients in the study to receive analgesics other than research drugs (indomethacin suppositories), which have been passed by the ethics Committee of Women's Hospital, School of Medicine Zhejiang University.

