### 6.2 Treatment Grouping

Twelve weeks of double-blind, randomization, placebo-controlled, parallel grouping. Subjects are randomized into 2 parallel dose groups and receive 10 mg of mifepristone tablets or placebo, one tablet daily, orally.

In the grouping process, the principle of randomization, allocation concealment, and double-blindness was used. The subject will receive a unique enrollment number, and the drug will also be assigned a unique number. The drug number will be pre-labeled on the package containing the study drug. The subject number and drug number are all unique and corresponding, and are handled by a special person and keep confidential for the clinician and the subject. This person does not participate in any part of the study of the trial. Neither the subject nor the investigator knows the characteristics of the assigned study drug. After the double-blind part is over, all subjects need to receive the same treatment.

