### (2) Case characteristics

Enrollment and completion: Summarize the number of cases enrolled and completed by each center, and list the unfinished cases and cases that do not enter each population.

Multi-center, Randomized, Double-blind, Controlled Study of the Effectiveness and Safety of  
Mifepristone in Treating Adenomyosis

(3) General information and baseline characteristics

The baseline is defined as Interview 1 (Day 0-3), and the SS is evaluated at baseline.

Baseline descriptions are made on the age, sex, allergy history, medication history, history of illness, and laboratory tests for each group of population.

(4) Analysis of safety indicators

The SS population is used for analysis.

Describe the number of occurrences of adverse events and adverse reactions of the total and each group and give the corresponding list in the detailed account.

Compared with the laboratory tests before the treatment, the situations after the treatment of each interview are described in the form of the crosstabs, and the abnormalities that are significant after the treatment are listed.

The vital signs indicators of each interview relative to the baseline during interviews and after treatment are described, and t-test or non-parametric test is used for intragroup comparison.

(5) Analysis of efficacy indicators

FAS and PP populations are used for analysis.

Baseline: Baseline description of each efficacy indicator.

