**Secondary effectiveness variable**

Pictorial blood loss assessment chart (PBAC), uterine volume and hemoglobin changes, and safety (e.g., adverse events, vaginal bleeding, gynecological safety).

The detailed analysis of secondary effectiveness variable is seen in the statistical analysis plan.

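### For uterine volume and the anemia indicators the protocol names only within-group before-after comparisons, which as written cannot show an effect over placebo

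*Protocol*

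**What the plan says.** Section 7.2.4 says that the anemia indicators, red cell count and hemoglobin, "are described and compared within group before and after treatment (0, 4, 12, 16weeks"). Section 7.2.3 says of the ultrasound measurements: "changes of the uterine volume were compared within group before and after treatment (0, 12, 24 weeks and follow-up period").

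Two of these measures carry a formal role. Section 2 states: "The secondary purpose is to evaluate the pictorial blood loss assessment chart (PBAC), uterine volume, hemoglobin changes". The paragraph on secondary effectiveness variables in 15.5 lists "Pictorial blood loss assessment chart (PBAC), uterine volume and hemoglobin changes, and safety". Red cell count appears as an efficacy measure only in 7.2.4.

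The same paragraph of 15.5 adds: "The detailed analysis of secondary effectiveness variable is seen in the statistical analysis plan". That plan is not at hand. The protocol itself gives a between-group method, ANCOVA with the baseline score as covariate, for the VAS pain score only.

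The design is described in 6.2 as "Twelve weeks of double-blind, randomization, placebo-controlled, parallel grouping".

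**The concern.** A before-after test within an arm asks whether that arm changed. It does not ask whether mifepristone changed the outcome more than placebo did, which is the question a placebo arm is there to answer. Section 1.1 justifies the trial by the lack of randomized, double-blind, controlled studies, and an uncontrolled before-after result would not fill that gap.

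The protocol itself leaves room for shared change. Section 6.8(1) forbids drugs for hemoglobin only when they are taken without a doctor's consent. Doctor-approved treatment can therefore raise hemoglobin in either arm, and a within-group test would count that rise as improvement. At stake is whether the trial can report a controlled result for two named secondary efficacy outcomes.

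**Working it through.** The plan gives no figure for these outcomes: no expected change, no SD of change and no power. There is therefore nothing of its own to reproduce, and the check measures how the named test behaves when the drug does nothing.

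**Inputs from the protocol**
- Two-sided tests at 0.05 (15.5, general principles).
- 60 evaluable subjects per arm, or 60 × 1.25 = 75 randomized per arm (15.5, sample size). These serve only as arm sizes here. Whether 60 suffices for the VAS comparison is a separate question.

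**Assumption**
- No drug effect, and the same true mean change c in both arms, in units of the SD of change. Because the documents give no value for c, the range 0 to 0.5 is shown.

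**Within-group test in the mifepristone arm** (normal approximation)

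P(significant) = 1 − Φ(1.96 − c√n) + Φ(−1.96 − c√n)

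Example with c = 0.3 and n = 60: c√n = 0.3 × 7.746 = 2.324. The first part is 1 − Φ(−0.364) = 0.642, and the second part is negligible.

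Example with c = 0.3 and n = 75: c√n = 0.3 × 8.660 = 2.598, which gives 0.738.

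| Equal change in both arms (SD) | n = 60 | n = 75 |
|---|---|---|
| 0 | 0.05 | 0.05 |
| 0.1 | 0.12 | 0.14 |
| 0.2 | 0.34 | 0.41 |
| 0.3 | 0.64 | 0.74 |
| 0.4 | 0.87 | 0.93 |
| 0.5 | 0.97 | 0.99 |

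The exact paired t-test gives nearly the same values, for example 0.63 and 0.73 at 0.3 SD.

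**Between-group test**

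The expected difference in change is c − c = 0 whatever c is, so the test rejects with probability 0.05, of which 0.025 favors mifepristone.

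**Are the data there?** Table 7-1 schedules the blood count and the pelvic ultrasound at screening and at weeks 4, 12 and 16, on one schedule for all subjects. A between-group comparison at week 12 needs no further measurement.

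**The case against.** The strongest reply is the deferral to the analysis plan. Sections 7.2.3 and 7.2.4 define the variables, neither says that the within-group comparison is the only one, and 15.5 sends the detailed analysis elsewhere. A between-group test may well stand there. This limits the point: a reader might infer that the trial discards its control arm or that the secondary purpose cannot be met, and the protocol alone does not show that. It does not remove the point. A deferral excuses silence, but here the protocol names a type of comparison. An analysis plan that follows it carries the weakness forward, and one that tests between arms departs from the protocol's wording.

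Section 2 claims superiority over placebo only for pelvic pain; the other outcomes are to be evaluated. That is a fair reason to rank the point lower, but not to leave the comparison uncontrolled.

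Other stronger readings also fail:
- *Regression to the mean as apparent benefit.* The entry limits exclude hemoglobin below 90 g/L and require a uterus smaller than at 10 weeks of pregnancy. Regression from those limits would tend to lower hemoglobin and enlarge the uterus, which is the opposite of apparent efficacy.
- *A known placebo effect on these outcomes.* Section 4.3 says: "The placebo control is necessary because of the more pronounced placebo effect observed in literature studies". It does not say for which outcome, and the sample-size text discusses placebo only for VAS.
- *Efficacy inferred from a significant result on drug and none on placebo.* That would be a misuse, but the protocol does not say it will reason so.
- *Vital signs.* In 15.5(4), "t-test or non-parametric test is used for intragroup comparison". This is a safety comparison, and the safety variables are otherwise to be analyzed descriptively. It is not part of an efficacy point.

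**Conclusion.** The point holds for 7.2.3 and 7.2.4. They name only a within-group comparison for uterine volume, red cell count and hemoglobin, and no other part of the protocol states a comparison with placebo for these measures. Followed as written, the tests cannot separate a drug effect from change common to both arms. With no drug effect, the chance of a significant result on mifepristone runs from 0.05 to 0.97 (n = 60) or 0.99 (n = 75).

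Those probabilities depend wholly on the assumed common change of 0 to 0.5 SD. They illustrate the range and do not predict what this trial will see. The logical point needs no assumption about size.

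The primary VAS analysis is between groups and unaffected. This should be fixed for the secondary outcomes, but it does not threaten the main conclusion.

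**What to change.** In 7.2.3 and 7.2.4, state as the main comparison the mifepristone-minus-placebo difference at week 12, from ANCOVA with the pre-treatment value as covariate, as already planned for VAS, with a 95% CI. Say which measurement is the pre-treatment value, since Table 7-1 schedules blood count and ultrasound at screening and not at the baseline visit. Keep the within-group changes as description without tests.

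Then check that the analysis plan says the same, and settle the wording before unblinding. While 7.2.3 is open, its week-24 time point should be reconciled with a visit schedule that ends at week 16; that is a separate inconsistency.

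The cost is wording and programming. No new data, visits or subjects are needed.
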